## Abstract

**Background:**

Cardiac rehabilitation (CR) uptake and adherence remain sub-optimal despite the apparent health benefits of modifying healthy behavior and slowing disease progression. eHealth is the use of information and communication technology (ICT) for health. eHealth lifestyle interventions and disease management have emerged as modalities to enhance CR accessibility, enable an individualized progress page, and enrich real-time contact, video-based information, and technology monitored functionality. This study aims to develop a nurse-led eHealth cardiac rehabilitation (NeCR) intervention and investigate its effectiveness on coronary heart disease (CHD) patients’ health outcomes.

**Methods:**

This single-blinded two-arm parallel randomized controlled trial will randomize 146 patients from the inpatient cardiovascular units of a hospital in Wuhan, China to receive either the NeCR or the usual care. The NeCR intervention uses a hybrid approach consisting of a brief face-to-face preparatory phase and an empowerment phase delivered by health technology. The preparatory phase aims at identifying self-care needs, developing a goal-oriented patient centered action plan, incorporating a peer support network and orientation to the use of the e-platform. The empowerment phase includes use of the multi-media interactive NeCR for promoting symptom management, monitoring lifestyle changes and offering psychological support. A tele-care platform is also integrated to enhance health care dialogue with health professionals and peer groups. The control group will receive the usual care. An evaluation of lifestyle behavioral changes, self-efficacy, health-related quality of life, anxiety and depression, cardiovascular risk parameters, and unplanned health services use will be conducted at baseline, 6 weeks and 12 weeks post-intervention.

**Discussion:**

This protocol proposes an individualized, comprehensive, and interactive NeCR delivered using a hybrid approach and guided by an empowerment model to optimize health outcomes of CHD patients. The intervention content and web-design is based on international health guidelines to improve credibility, comprehensibility and implementation. This study also proposes a new method of peer support in which the researcher shares participants’ progress toward goal attainment with the peer group. Results of this research have the potential to increase accessibility and availability of CR, improve cardiac rehabilitation service development in China, and inform eHealth lifestyle interventions.

**Trial registration:**

Chinese Clinical Trial Registry: ChiCTR1800020411; Date of registration: December 28, 2018.

## Background

Coronary heart disease (CHD) is the accumulation of plaque in coronary arteries that limits blood perfusion of the heart [1]. It is related to cumulative exposure to risk factors as well as aging such that 40-year old men and women have a 49 and 32% lifetime risk of developing CHD, respectively [2, 3]. An epidemiologic study indicated that patients with CHD had higher exposure to unhealthy lifestyle behaviors, and physiological and psychosocial risk factors [4]. Using effective behavioral change interventions to address these risk factors could prevent 75% of cardiac events and slow disease progression to heart failure or even death [5]. Current health statistics report 7.4 million deaths globally due to CHD and predict CHD will be the leading cause of disability by 2020 [6].

International guidelines strongly recommend cardiac rehabilitation (CR) programs to manage modifiable risk factors and improve health outcomes of CHD patients. The core components of CR incorporate physical exercise, patient education on lifestyle changes, disease management and psychosocial support [1, 7]. Indeed, CR is a structured program not only addressing direct CHD management but also other conditions including hypertension, dyslipidemia, diabetes and obesity. Substantial benefits associated with CR include reducing mortality by 20 to 47%, reducing hospital re-admission by 18%, improving physical activity, reducing cardiovascular risk factors and improving quality of life [1, 8–10].

Despite the apparent health benefits, 62% of countries do not offer CR, due to non-compatible health and social policy, inadequate infrastructure and manpower [11]. Rate of participation in and adherence to CR is also low and ranges from 14 to 35.5%, due to inadequate access and time conflicts with other life activities [12, 13].

eHealth CR refers to the delivery of CR through information and communication technology (ICT), which has evolved as an alternative modality to improve availability and accessibility of CR. This mode includes a website, mobile applications, monitoring sensors, email, phone calls and short message services [14]. These make eHealth CR unique in being able to promote health behaviors in real-time so that participants can access information, upload self-monitored health data, receive automated feedback, and connect with peers or healthcare professionals [15]. eHealth CR also has the potential of being individually tailored to accommodate individual risk factors, goals and progresses using personal webpage for health behavior change [16]. It also enables experimental teaching that provides video-based health information to facilitate skill building. This modality is based on the statistic that 55.1% of the world’s total population are Internet users [17]. Increasing participatory Internet use has been reported among older adults and become an important health information source and patient empowerment medium for health decision making and behaviors [18]. For this reason, there is increased advocacy to integrate eHealth platforms to deliver care components of CR to address the resource deficiency in traditional CR and provide more accessible and individualized health care to cardiac patients to improve health outcomes.

Existing evidence indicates high feasibility and acceptability of the e-platform to deliver CR [14, 15]. A systematic review and meta-analysis was conducted to examine the effectiveness of eHealth CR on CHD patients [19]. Among the 14 studies reviewed [14, 20–32], meta-analysis indicated that eHealth CR led to significant improvement in physical activity, quality of life and re-hospitalization. There were inconclusive effects on diet, smoking, anxiety and depression, and other physiological risk parameters. This may be due to a lack of emphasis on promoting stress management, smoking cessation and symptom management among the study participants. As compared with studies which reported positive therapeutic effects on health behavioral outcomes, the studies which reported no positive effects were also less likely to incorporate the core strategies of patient empowerment to facilitate health behavioral changes. Such strategies are based on social cognitive theory and refer to individualized cardiovascular risk assessment, goal attainment process and enhanced self-directed tele-monitoring with professional feedback [19–24]. This review provides important insights on how to develop a more promising eHealth CR to enhance behavioral, psychological, physiological and clinical outcomes. All the identified studies in the review were conducted in developed countries including Australia [20], Belgium [21], Canada [22, 23], New Zealand [24, 25], Norway [26], Netherlands [27], Sweden [28], United Kingdom [29, 30], and the United States [14, 31, 32]. None were conducted in Asia/ China, where the cultural difference in health and illness behaviors and relationships with the health care system may limit the generalizability of the findings. China has 772 million Internet users with a penetration rate of 55.8 and 73% nationally and in urban areas, respectively [33]. The ability of older Chinese adults to use an eHealth intervention depends largely on a friendly webpage design, perceived usefulness and culture-compatible components [34, 35]. Therefore, a randomized controlled trial is needed to investigate the effects of an individualized, empowerment-based, and culturally adjusted eHealth CR program to improve health outcomes for people with CHD.

### Social cognitive theory and patient empowerment

The design of this eHealth CR is underpinned by social cognitive theory and patient empowerment model to enhance the translation of online input to actual health behavioral changes [36, 37]. This model uses a patient-centered collaborative approach that patients’ perspectives, ability and resources will be assessed and integrated into formulating self-care goals and action plan. Interactive teaching and experimental learning will be used to enhance patients’ knowledge and skills acquisition as well as transferring the knowledge and skills into behavior change. Self-regulation is also important as patients use proximal and distal goals to guide their behavior and monitor their health behavior and the circumstances under which it occurs.

### Aims

This aims of the study are to develop a nurse-led eHealth cardiac rehabilitation (NeCR) intervention and investigate its effects on lifestyle behavior, self-efficacy, health-related quality of life, anxiety and depression, cardiovascular risk parameters and unplanned health services use.

## Methods

The study design is a single-blinded two-arm parallel randomized controlled trial comparing the effects of an eHealth CR with usual care on the behavioral and clinical outcomes of patients with CHD who are admitted for disease exacerbation.

### Study sample

The study will be conducted at four cardiology units of Tongji Hospital, Wuhan, China where CHD patients are treated conservatively with percutaneous coronary intervention (PCI) or medication and discharged under stable medication regimen. Eligibility requirements of participants are: adults aged 18 years or older; hospitalized for an initial diagnosis of CHD based on angiography or exacerbation of this condition in previously diagnosed cases; anticipated discharge to home; uses a computer and/or smartphone to access the Internet at home, reads and speaks Mandarin; minimum of primary education level; and no prescribed activity or exercise restriction. Exclusion criteria are: a diagnosis of acute psychotic disease/ life-limiting condition; absolute and relative contradictions to exercise testing and training and high risk for exercise prescription according to the American Association of Cardiovascular and Pulmonary Rehabilitation (AACVPR) guideline; and, having auditory, visual, fine motor, or ambulatory disorders.

Referring to a systematic review of studies which examined the effects of tele-cardiac rehabilitation on lifestyle behaviors, health outcomes and quality of life, the effects size on promoting healthy lifestyle is 0.42 to 1.29 so that a medium effect size of 0.5 (with 80% power and .05 significance) is conservatively adopted in this study [38]. The estimated sample size is 146, which takes into consideration an expected attrition rate of 12% based on prior studies with similar post-test time points of 6–12 weeks [31, 39]. Eligible participants will be identified by research nurses from four inpatient cardiac departments of the hospital by reviewing medical records. A second confirmation will be made with the on-site physicians. Eligible participants will then be invited to participate in this study and an information sheet will be provided. After obtaining informed consent, baseline data will be collected.

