The goal setting for exercise will indicate the frequency, duration, and intensity of exercise to gradually achieve at least 150 min of moderate weekly exercise. The nurse will also teach the participants about using Borg’s ratings of perceived exertion to achieve the desired intensity with a perceived exertion of 12 to 14 (“somewhat hard” on a scale of 6 to 20) [51]. For dietary habits, a guideline based culturally appropriate 10-item dietary habit checklist has been developed assessing food intake, cooking methods, eating pattern, and method of eating in restaurants. This checklist is adapted from the dietary checklist designed by the Department of Health in Taiwan to guide the dietary modification for cardiac patients [52]. The research team has modified the content so as to make it culturally relevant to the CHD patients in China. The revised content has been validated by two Chinese dietitians. Participants will be supported in setting successive goals to eventually attain over 90% adherence to this checklist. As for stress management, participants will be supported to set goals of managing stress below a level of 3 as assessed by 0–9 scored scale [53]. The nurse will collaborate with the patients to work out the action plan with a variety of exercise, dietary and relaxation skills options. Participants who smoke will also be supported to set a cessation goal and provided with tips such as nicotine replacement therapy, avoid smoking for social influences and managing stress [54]. A written participant-centered goal-driven action plan and information handout for self-management will be provided to reinforce knowledge retention. The individualized goals and action plan will be uploaded to the participants’ password protected personal webpages on the eHealth CR platform.

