### Randomization and data collection procedure

Eligible patients will be invited to participate in this study and an information sheet will be provided. After obtaining informed consent, baseline data will be collected. Participants will be randomly assigned to either the intervention or control group by block randomization. Three different block sizes of 4, 6 and 8 will be used. The random number for group assignment will be generated by random allocation software. The group assignment will be written and placed in an opaque sealed envelope and given to participants by the research assistant after baseline data collection (T_0_). Outcome evaluation will take place at the 6-week intervention (T_1_) and upon completion of the 12-week intervention (T_2_) by trained research assistants who are blinded as to the participants’ intervention allocation (Fig. 1). Participants will not be blinded as to their group allocation. The following parameters for outcome assessment will be used to include health behavior, emotional outcomes, health-related quality of life, cardiac physiological risk parameters and unplanned health services use. Participants’ travel expenses for data collection will be reimbursed.

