### Primary outcomes

The primary outcomes focus on health behavioral change including physical activity, health promoting lifestyle habits, and smoking behaviors. Physical activity is defined as movement of the body that uses energy. Objectively, physical activity level will be measured by the pedometer (Mi Band, China) record of step count for three weekdays [57]. A pedometer correlates strongly with different accelerometers (median r = 0.86) as well as the time in observed activity (median r = 0.82) [58]. The International Physical Activity Questionnaire (IPAQ) will be used to comprehensively assess the self-reported time spent in walking, light/moderate/rigorous exercise and sitting across various domains using 27 items. The IPAQ has test–retest reliability with intra-class correlation coefficients of 0·74 to 0·97 for each sub-domain for Chinese adults [59]. Total physical activity measured by the IPAQ was moderately correlated with pedometer measured exercise levels (r = 0.46) [60].

Health promoting behaviors will be measured by the Health Promoting Lifestyle Profile II (HPLP- II) [61]. The HPLP- II measures six aspects of health promotion behaviors including nutrition, interpersonal support, stress management, exercise, health responsibility and self-actualization. The HPLP - II has good internal consistency with 0.92 for the entire scale and 0.69–0.84. The HPLP uses a four-point scale with 1–4 representing always to never with a total score ranging from 40 to 160 and a higher score indicating better health behavior. The HPLP-II has been translated and validated into Chinese with Cronbach’s α coefficient of 0.63 to 0.81 [62].

Smoking status will be asked to evaluate the abstinence rate using two questions: (1) what is your current smoking status? (current smoker, ex-smoker or nonsmoker) (2) How many cigarettes do you smoke per day? [63].

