### Data analysis

The latest version of SPSS will be used to analyze data with a 5% significance level (two-sided). Treatment evaluation will be performed based on the principle of intention to treat. A generalized estimating equations (GEE) model will be used to compare the differential between the two groups related to each of the outcomes across the time-points, with adjustment for potential confounding variables in order to obtain a more precise estimation of intervention effect. The potential confounding variables will be selected on the basis of clinical judgment and statistical incomparability at baseline. For the smoking behavior as nominal data, the Chi-square test will be used to compare the number of patients who quit smoking between the groups. In addition, the Friedman test will be used to compare the changes in percentage of smoking cessation among the groups over time [73]. Survival analysis, the analysis of time-to-event data will be conducted to describe the length of time from entering the program to an unplanned health services utilization.

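### The single 80% power statement behind N = 146 does not hold for smoking cessation, a primary outcome to which only baseline smokers can contribute

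*Protocol article*

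**What the plan says.** The protocol article contains one sample-size calculation, under Study sample. Its effect size comes from a review in which "the effects size on promoting healthy lifestyle is 0.42 to 1.29", and from this "a medium effect size of 0.5 (with 80% power and .05 significance) is conservatively adopted in this study". The total and the attrition follow: "The estimated sample size is 146, which takes into consideration an expected attrition rate of 12" per cent. Data analysis makes the 5% level two-sided. The power sentence names no outcome.

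Under Primary outcomes: "The primary outcomes focus on health behavioral change including physical activity, health promoting lifestyle habits, and smoking behaviors". The three are not ranked. Smoking is recorded by asking whether the patient is a current smoker, an ex-smoker or a nonsmoker, and how many cigarettes are smoked per day.

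Under Data analysis, the test for smoking is fixed: "the Chi-square test will be used to compare the number of patients who quit smoking between the groups". A Friedman test of cessation over time is added.

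The eligibility criteria under Study sample do not mention smoking. The intervention sections treat smokers as a subgroup: "Participants who smoke will also be supported to set a cessation goal", and the self-monitoring section asks for updates of smoking status only where applicable.

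**The concern.** A comparison of means with 64 completers per arm uses a measurement from every one of them. A comparison of quitters does not, because an ex-smoker or nonsmoker at baseline cannot quit. If only some of the sample smoke, the informative number for this primary outcome is that fraction of 128, while the only power figure in the document is 80%.

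What is at stake is how a negative result is read. With low power, a non-significant smoking comparison is likely even if the programme works. A reader who sets it against the stated 80% could conclude that the programme does not help smokers quit. The article's own Background calls earlier evidence on smoking inconclusive, so this is a question on which a misread null would matter.

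**Working it through.** **Inputs from the document.** Standardised effect 0.5, power 80%, two-sided 5%, attrition 12%, N = 146 (Study sample; Data analysis). Two arms with even block sizes ("Three different block sizes of 4, 6 and 8 will be used"); equal allocation is assumed, as no ratio is stated.

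**Inputs assumed.** The share of baseline smokers (20% to 60%, with 100% as reference) and the cessation effect. As the counterpart of d = 0.5, I use Cohen's h = 2·arcsin√p₂ − 2·arcsin√p₁ = 0.5; for example, 30% against 54% quitting.

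**Step 1: reproduce 146.** A two-sample t-test at d = 0.5 needs 63.8, so 64 per arm or 128 in total. Then 128 / 0.88 = 145.5, rounded up to 146. The stated figure reproduces exactly. The normal approximation gives 63 per arm and 126 / 0.88 = 143.2, so 144.

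**Step 2: power for the smoking comparison.** Completers per arm are 146 × 0.88 / 2 = 64.24. With smoker share f, smokers per arm are m = 64.24·f, and power ≈ Φ(h·√(m/2) − 1.96). For f = 0.4: m = 25.7 and 0.5 × √12.85 − 1.96 = −0.17, so power is 43%.

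| Share who smoke | Smokers per arm | Power, h = 0.5 | Power, 30% vs 50% quitting |
|---|---|---|---|
| 20% | 13 | 24% | 17% |
| 30% | 19 | 34% | 24% |
| 40% | 26 | 43% | 31% |
| 50% | 32 | 52% | 37% |
| 60% | 39 | 59% | 43% |
| 100% | 64 | 81% | 64% |

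Exact enumeration of the uncorrected chi-square at 30% vs 54.4% gives 30%, 35%, 43%, 54% and 81% for 13, 19, 26, 32 and 64 smokers per arm. The approximation is therefore adequate, though a little low in the smallest groups.

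**Step 3: other denominators.**
- No loss to attrition (73 per arm), with h = 0.5 kept: 38%, 48% and 57% at 30%, 40% and 50% smokers.
- All 64 completers per arm as denominator, with 30% vs 54.4% quitting among smokers: 17%, 23%, 31% and 39% at 20%, 30%, 40% and 50% smokers. Including non-smokers dilutes the contrast.

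**Step 4: effect needed for 80%.** h = (1.96 + 0.84)·√(2/m). This gives 0.90 at 30% smokers (m = 19.3), 0.78 at 40% (m = 25.7) and 0.70 at 50% (m = 32.1). From a 30% quit rate, h = 0.90 means about 74% quitting in the other arm.

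**Step 5: what resizing would take.** For 30% vs 50% quitting, 80% power needs 93 smokers per arm, 186 in total. With 12% attrition and 40% smokers, that is 186 / 0.88 / 0.4 = 528.4, so 529 patients.

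**The case against.** The strongest reply is that the article never claims 80% power for smoking. The effect size is drawn from a range for lifestyle promotion, which fits the HPLP-II, and a fair reader could take the calculation as meant for that outcome. This stands in part: a reader might infer that the authors asserted 80% for cessation explicitly, and the text does not show that. But the power sentence is not tied to one outcome, it is the only one in the document, and smoking sits beside the HPLP-II as an unranked primary. The restriction has to be guessed.

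A second stronger inference is that 146 is miscalculated. It is not; it reproduces exactly for a continuous outcome.

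Third, the size of the shortfall rests on assumptions. This is true of the smoker share and of treating d = 0.5 as h = 0.5. Values of h from 0.7 to 0.9 lie numerically inside the cited range of 0.42 to 1.29 and would give 80% at 50% to 30% smokers. But that range is not for cessation, and 0.5 is the value the plan adopted.

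Fourth, a condensed article may leave outcome-specific power notes to the full protocol or the SAP. A missing note would indeed be no finding. Here, however, the sample-size statement, the primary status and the test are all printed, and together they do not fit.

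Fifth, smoking is also covered by cigarettes per day and a Friedman test. Neither increases the number of patients who can quit.

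Finally, nothing in the article says that a null smoking result will be read as no effect. That harm is a risk, not a stated intention.

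**Conclusion.** The concern holds in a limited form. N = 146 is correct for a two-group comparison of a continuous outcome measured in all 128 completers. The unqualified 80% does not carry over to smoking cessation, which the plan makes a primary outcome and tests on quitters. At the plan's own nominal effect, and assuming 20% to 60% baseline smokers, power is about 24% to 59%. At h = 0.5 it reaches 80% only if nearly everyone smokes; at lower shares a clearly larger effect is needed.

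These figures rest on four assumptions: the inferred means formula, equal allocation, the smoker share, and h = 0.5 as the counterpart of d = 0.5. The direction does not depend on the exact share: for a given effect, any share clearly below 100% lowers power relative to a comparison using every completer.

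It might also be inferred that smoking must lose its primary status. The documents do not compel that. It is a design choice, and the mismatch can be removed without it.

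**What to change.** In Study sample, state that 80% power at d = 0.5 with 128 completers applies to a continuous lifestyle outcome measured in all patients, such as the HPLP-II, and not to smoking cessation.

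In Data analysis, specify that cessation is analysed among baseline smokers as a difference in quit proportions with a 95% confidence interval. Add that the trial is not powered for this comparison and that a non-significant result will not be read as absence of effect.

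The cost is a few sentences, communicated to the ethics committees as the article's Ethics approval section requires for protocol modifications. No extra patients or procedures are needed, and N is unchanged. The power claim becomes narrower, which is the purpose. Moving smoking to the secondary outcomes is optional; as it changes a primary outcome of a registered trial, it would need a registry update as well as ethics notification.

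### The planning effect size of 0.5 is called conservative, but it lies above the lower end (0.42) of the range cited to justify it; the calculation of 146 is itself correct

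*Protocol article*

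**What the plan says.** All statements are in the protocol article.

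- **Study sample, source of the effect size.** From a systematic review of tele-cardiac rehabilitation, "the effects size on promoting healthy lifestyle is 0.42 to 1.29".
- **Study sample, planning value.** From that range the protocol infers that "a medium effect size of 0.5 (with 80% power and .05 significance) is conservatively adopted in this study".
- **Study sample, attrition.** The total of 146 allows for "an expected attrition rate of 12% based on prior studies with similar post-test time points of 6–12 weeks".
- **Data analysis, test level.** Data are analysed "with a 5% significance level (two-sided"). Outcomes are compared between groups across the time points by GEE, adjusted for confounders picked by clinical judgment and by lack of comparability at baseline.
- **Randomization and data collection procedure.** Outcomes are assessed at baseline (T0), 6 weeks (T1) and 12 weeks (T2). The allocation ratio is not printed; "Three different block sizes of 4, 6 and 8 will be used", which is compatible with 1:1.

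**The concern.** The sentence presents the cited range as the reason for the planning value and then describes that value as conservative. A reader will take this to mean that power is protected against the less favourable part of the evidence. But 0.5 is larger than 0.42, so at the bottom of the range the trial has less than its nominal power.

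The stake is how a null result would be read. Someone told that the trial was conservatively powered may take a non-significant primary outcome as fair evidence against the intervention. If the true effect were 0.42, the unadjusted comparison would miss it about 35% of the time, against about 20% at 0.5.

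**Working it through.** **Inputs.** d = 0.5, range 0.42 to 1.29, 80% power, 5% level, 12% attrition and N = 146 come from Study sample; two-sided testing comes from Data analysis. Assumptions: 1:1 allocation, and an unadjusted two-sample t test at one time point. The number of completers is derived, not printed: 146 × 0.88 = 128.5, taken as 128, or 64 per arm.

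**Step 1: reproduce the protocol's figure.** By the normal approximation, n per arm = 2(1.960 + 0.842)² / d² = 2 × 7.85 / 0.25 = 62.8. The t test raises this to 63.8, so 64 per arm and 128 in total. Allowing for attrition, 128 / 0.88 = 145.5, so 146. This matches exactly. Power at d = 0.5 with 64 per arm is 80.1%, and the smallest effect detectable with 80% power is 0.499. The design therefore has no margin below 0.5.

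**Step 2: power at the lower end of the range.** The noncentrality is d√(n/2), with n per arm.

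| d | n per arm | Noncentrality | Power (t test) |
|---|---|---|---|
| 0.50 | 64 | 0.50 × √32 = 2.83 | 80.1% |
| 0.42 | 64 | 0.42 × √32 = 2.38 | 65.5% |
| 0.42 | 73 (no attrition) | 0.42 × √36.5 = 2.54 | 71.2% |

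For scale, 80% power at 0.42 needs 90 per arm by the t test. Then 90 / 0.88 = 102.3, so 103 per arm or 206 randomised.

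**Step 3: what adjustment for the outcome's own baseline could recover.** If the T0–T2 correlation is r, adjustment multiplies the residual SD by √(1 − r²), so the effective d is 0.42 / √(1 − r²). With 64 per arm:

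| Assumed r | Effective d | Power at 0.42 |
|---|---|---|
| 0.30 | 0.440 | 70% |
| 0.40 | 0.458 | 73% |
| 0.50 | 0.485 | 78% |
| 0.54 | 0.499 | 80% |
| 0.60 | 0.525 | 84% |

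The protocol gives no correlation, so r is shown as a range.

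**Step 4: why the form of the adjustment matters.** If T0 stays in the model as a freely estimated response and the group-by-time contrast is tested, the comparison behaves like one of change scores, with effective d = 0.42 / √(2(1 − r)). At r = 0.5 this is 0.42 / 1 = 0.42, no gain over Step 2, and for smaller r power falls below 65%.

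**The case against.** **The 80% is not wrong.** A reader might infer that the trial has 65% power instead of the 80% it claims. The document does not support that. It attaches 80% to d = 0.5 only, and that figure is correct. Nowhere does it claim 80% at 0.42. This objection stands in full: there is no arithmetic error.

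**0.5 is low within the range.** It lies (0.50 − 0.42) / (1.29 − 0.42) = 0.08 / 0.87, about 9% of the way up. Against most of the range it is a cautious choice, and the protocol prints 0.42 in the same sentence, so nothing is hidden. This stands in part. It limits the seriousness, but the word still fails at the lower end, which is where a conservative choice should protect.

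**The meaning of the range is unclear.** The protocol does not say whether its ends are single-study estimates, pooled estimates for different behaviours or confidence limits. It therefore cannot be argued that the trial had to be sized at 0.42. This stands, and no increase in N is proposed.

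**65% is not the power of the planned analysis.** That analysis is an adjusted GEE over several time points, and its power could be higher or lower depending on correlations that are not given. This stands, so the figure must carry its label. It does not rescue the wording, because the protocol's rule for choosing covariates does not ensure that each outcome is adjusted for its own baseline.

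**Covariates may be left to the SAP.** Often they are. Here, however, the protocol already states a selection rule, and that rule depends on observed baseline imbalance.

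**Conclusion.** The point holds as an error of justification. The value 0.5 is not conservative against the lower end of the cited range of 0.42 to 1.29. The sample size of 146 and its 80% power at d = 0.5 are correctly calculated. At d = 0.42 an unadjusted t test at one time point has about 65% power with about 128 completers, and about 71% if all 146 are retained. These figures assume 1:1 allocation, a two-sided 5% level and completers derived from the 12% attrition.

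The trial is not shown to be invalid or to need more patients. Severity is minor to moderate: the wording costs almost nothing to correct, and the adjustment rule offers a real but unquantified gain.

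**What to change.** 1. **Wording, Study sample.** Keep N at 146 and delete *conservatively*. State that 146 randomised (about 128 completers) give 80% power at d = 0.5 and about 65% at d = 0.42, the lower end of the cited range, for an unadjusted two-group comparison at one time point.
2. **Analysis, Data analysis.** Prespecify that each continuous primary outcome is adjusted for its own T0 value whatever the observed baseline balance, in place of choosing covariates by baseline incomparability. Use T1 and T2 only as responses, or keep T0 as a response with baseline means constrained equal across arms. Do not enter T0 both as a covariate and as a freely modelled response.
3. **Do not promise 80% at 0.42.** Recovery to that level needs a T0–T2 correlation of about 0.54 or more, for which the protocol gives no evidence.

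**Cost.** A revised sentence and a fixed model specification. No extra patients or measurements are needed, since T0 is already collected. The stated power will look less favourable at the low end of the range.
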